### **5.7.2. In the community**

Up to Clinic Visit 6 (approximately one month post Dose 3) volunteers will be seen at least monthly at clinic visits, and for 6 days following each dose. After Clinic Visit 6 (i.e. during the single-blind phase of the study) capture of SAEs will be enhanced by means of monthly visits by field workers and a final Clinic Visit at Month 14 (Clinic Visit 7).

During the field worker visits, the children's parent(s)/guardian(s) will be asked retrospectively if any SAEs occurred since the last visit and this information will be recorded. Unreported SAEs detected in this way will be investigated and reported by the Principal Investigator or delegate on the corresponding SAE forms (see Section 5.8). In the case of a death which has occurred at home, supplementary information will be gained using the verbal autopsy technique. The verbal autopsy will be conducted according to previously published methods and detailed in the SOPs on file with the investigators [Smith 1991].

If any child is reported to be unwell at the time of a visit, the field worker will advise the parent(s)/guardian(s) to seek care at HAS. In the event that a child is seriously ill, the field worker will inform the Principal Investigator or designate, and transport will be arranged to HAS, if judged appropriate by the responsible clinician.

### **5.8. Provision of health care**

In order to maximize capture of adverse events parents/guardians will be encouraged to bring their children for all primary health care to the MRU of HAS. To facilitate this, the study will reimburse parents/guardians for the costs of bringing their children to the hospital. This strategy has been successfully implemented in trials carried out by HAS MRU.

Contact details for the PI will be provided to parent(s)/guardians(s) on the ICF. Medical attention is available on a 24-hour basis, seven days a week at HAS. Children requiring hospitalization will be admitted to the pediatric ward of the HAS. Care there will be provided collaboratively by MRU physicians and HAS pediatric clinical staff. The diagnostic and treatment facilities available at HAS are described in Section 4.4.

Children requiring specialized care or investigation unavailable at HAS such as treatment of complex renal insufficiency, endocrine abnormalities or malignancies will be transported Centre Hospitalier de Libreville. If this is considered necessary by the supervising clinician, HAS will facilitate the transfer of study subjects to Centre Hospitalier de Libreville.

If a volunteer is found to have a medical condition that excludes them from participation in the trial (whether diagnosed during screening or during the trial), their parent(s)/guardian(s) will be informed at a private appointment with a member of the clinical staff of the research team. The clinical staff member will take as much time as is required to explain the condition, including its severity, potential causes, long-term implications, impact on current and future lifestyle of both the child and the parent(s)/guardian(s) and evaluation and treatment options. Once it is clear that the parent(s)/guardian(s) understand the medical condition, the clinical staff member will develop an evaluation and treatment plan with the parent(s)/guardian(s) and ensure that the options are understood.

If the clinical staff member feels that the subject requires specialty or sub-specialty care, HAS will coordinate with the relevant physician and parent(s)/guardian(s) to make an appointment and provide transportation to the appointment if necessary. All history, physical examination and laboratory findings available will be provided to the parent(s)/guardian(s) and the referral physician.

Treatment for all medical conditions will be given according to the standard treatment regimens of Gabon. Any expenses — including transport — incurred by the parents/guardians of study participants for clinical care related to acute conditions will be borne by the study. Long-term care for chronic conditions unrelated to study procedures will be delivered following local guidelines with no financial support from the study.

A detailed description of the healthcare system available in the study area is provided in Section 4.4.

### **5.8.1. Management and treatment of malaria in all subjects**

All children with suspected malaria will have a blood sample taken for confirmation of infection. Children with malaria that can be treated with oral medication will receive a 6-dose regimen of Coartem® (artemether/lumefantrine, Novartis AG, Zurich, Switzerland), as advocated by WHO [World Health Organization 2005] and the government of Gabon.

Children who require inpatient care or systemic treatment will receive treatment with intravenous quinine, which is standard practice and effective therapy in Gabon.

#### **5.8.1.1. Insecticide impregnated bednets**

An insecticide impregnated bednet will be offered to all parent(s)/guardian(s) who present their child for screening regardless of whether or not their child takes part in the trial. Parents/guardians will be instructed on the proper use and maintenance of insecticide impregnated bednets.

## **5.9. Subject identification**

Subject numbers will be issued sequentially to subjects at screening. Treatment numbers are assigned at the time of Dose 1 in order of administration of dose.

Subject numbers will be issued consecutively to all children who are consented for screening. To identify the child at subsequent contacts, each child's parent(s)/guardian(s) will be issued with an identification card with the picture of the parent(s)/guardian(s) with the child attached to it.

Vials of RTS,S/AS02D and RTS,S/AS01E will be identified by a treatment number. The unique treatment number will identify all doses of the vaccine administered to each subject. The treatment number will be issued sequentially at Clinic Visit 2. The treatment number will be recorded on the clinic form and subsequently the case report form documenting the linkage between the subject number and the treatment number.

## 5.10. Outline of study procedures

**Table 3 List of study procedures**

|                                                                             | SCREEN         | DOUBLE-BLIND PHASE |                |                |                |                |                |                |                | SINGLE-BLIND PHASE |                |
|-----------------------------------------------------------------------------|----------------|--------------------|----------------|----------------|----------------|----------------|----------------|----------------|----------------|--------------------|----------------|
| Study Month                                                                 |                | Month 0            |                |                | Month 1        |                | Month 2        |                | Month 3        | Month 4 to 13      | Month 14       |
| Study Day                                                                   | -28 to 0       | 0                  | 1 to 5         | 6              | 30             | 31 to 36       | 60             | 61 to 66       | 90             |                    |                |
| Clinic Visit                                                                | 1              | 2                  |                | 3              | 4              |                | 5              |                | 6              |                    | 7              |
| Field Worker Visit Code #                                                   |                |                    | 21 to 25       |                |                | 26 to 31       |                | 32 to 37       |                | 38 to 47           |                |
| STUDY PROCEDURES                                                     |                |                    |                |                |                |                |                |                |                |                    |                |
| Informed consent                                                            | ●              |                    |                |                |                |                |                |                |                |                    |                |
| Medical history                                                             | ○              | ●                  |                |                |                |                |                |                |                |                    |                |
| Record HBV immunization status                                              | ●              |                    |                |                |                |                |                |                |                |                    |                |
| Vital signs                                                                 | ○              | ●                  |                | ○              | ○              |                | ○              |                | ○              |                    | ○              |
| Complete physical examination                                               | ○              | ●                  |                |                |                |                |                |                |                |                    |                |
| Measure body weight                                                         | ○              | ●                  |                |                | ○              |                | ○              |                | ○              |                    | ○              |
| Assign Subject Number                                                       | ●              |                    |                |                |                |                |                |                |                |                    |                |
| Prevaccination temperature                                                  |                | ●                  |                |                | ●              |                | ●              |                |                |                    |                |
| Check inclusion/exclusion criteria                                          | ●              | ○                  |                |                |                |                |                |                |                |                    |                |
| Check elimination criteria                                                  |                | ●                  |                | ●              | ●              |                | ●              |                | ●              |                    | ●              |
| Check contraindications to vaccination                                      |                | ●                  |                |                | ●              |                | ●              |                |                |                    |                |
| Randomization                                                               |                | ●                  |                |                |                |                |                |                |                |                    |                |
| Administer RTS,S/AS01E or RTS,S/AS02D vaccine                               |                | ●                  |                |                | ●              |                | ●              |                |                |                    |                |
| Recording of concomitant medication                                         |                | ● c     | ● c | ● c | ● c | ● c | ● c | ● c | ● c | ● d     | ● d |
| SAFETY DATA COLLECTION                                               |                |                    |                |                |                |                |                |                |                |                    |                |
| Recording of solicited symptoms (Investigator)                              |                | ●                  |                | ●              | ●              |                | ●              |                |                |                    |                |
| Recording of solicited symptoms (Field Workers)                             |                |                    | ●              |                |                | ●              |                | ●              |                |                    |                |
| Recording of unsolicited AEs within 1 month post-vaccination (Investigator) |                | ●                  |                | ●              | ●              |                | ●              |                | ●              |                    |                |
| Morbidity surveillance/recording of SAEs                                    | ● b | ●                  | ●              | ●              | ●              | ●              | ●              | ●              | ●              | ●                  | ●              |
| Monthly field worker home visits                                            |                |                    |                |                |                |                |                |                |                | ●                  |                |
| SAFETY LABS                                                          |                |                    |                |                |                |                |                |                |                |                    |                |
| Complete blood count a                                           | ●              |                    |                | ●              |                |                |                |                | ●              |                    | ●              |
| Creatinine, ALT, bilirubin                                                  | ●              |                    |                | ●              |                |                |                |                | ●              |                    | ●              |
| INVESTIGATIONAL ASSAYS                                               |                |                    |                |                |                |                |                |                |                |                    |                |
| Anti-HBs antibodies                                                         | ●              |                    |                |                |                |                | ●              |                | ●              |                    | ●              |
| Anti-CS antibodies                                                          | ●              |                    |                |                |                |                | ●              |                | ●              |                    | ●              |
| Cell-Mediated Immunity and B-cell Memory                                    | ●              |                    |                |                |                |                | ●              |                | ●              |                    | ●              |
| FINAL ANALYSIS                                                       |                |                    |                |                |                |                |                |                |                |                    |                |
| STUDY CONCLUSION                                                     |                |                    |                |                |                |                |                |                |                |                    |                |

#: Field Worker visit code numbers not necessarily sequential. ● is used to indicate a study procedure that requires documentation in the individual CRF and ○ is used to indicate a study procedure that does not require documentation in the individual CRF.

a: includes analysis of hemoglobin, total white cell count and platelets

b: SAEs related to study procedures will be collected

c: all medications required by protocol to be recorded at these visits

d: record administration of immunosuppressants or other immune-modifying drugs during this period (for corticosteroids this means prednisone or equivalent,  $\geq 0.5$  mg/kg/day. Inhaled or topical steroids are allowed and should not be recorded. ALSO all immunoglobulins and blood products should be recorded during this period.

It is the investigator's responsibility to ensure that the intervals between visits/contacts are strictly followed. These intervals determine each subject's evaluability in the according to protocol analyses (see Sections 4.6 to 4.9 and Section 10.6 for details of criteria for evaluability and cohorts to be analyzed). The intervals are tabulated in Table 4.

**Table 4 Intervals between study stages/visits**

| Interval          | Length of interval      |
|-------------------|-------------------------|
| (Visit 1→Visit 2) | Screening –28 to Day –0 |
| (Visit 2→Visit 4) | 21 to 35 days           |
| (Visit 4→Visit 5) | 21 to 35 days           |
| (Visit 2→Visit 7) | 14 months ± 1 month     |

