**Study design**

- Experimental design: Phase II, single center, double-blind (observer blind, participant blind), randomized (1:1 ratio) trial with two groups in one study site.

- Healthy male and female children aged 18 months to 4 years of age will be screened; those determined to be eligible, based on the inclusion and exclusion criteria, will be enrolled in the study.
- Route of administration: all vaccines will be administered by the intramuscular route to the left deltoid.
- Each child will be observed for at least 60 minutes after vaccination to evaluate and treat any acute adverse events (AEs).
- There will be a 7-day follow-up period for solicited AEs post-vaccination: Day 0 evaluation will be carried out by the study physician at the study center. Subsequently, trained field workers will visit the children to solicit AEs on days 1 to 6 after each vaccination (evaluation on Day 6 post Dose 1 will be carried out by the study physician at the study center).
- There will be a 30-day (day of vaccination and 29 subsequent days) follow-up after each vaccine dose for reporting unsolicited symptoms.
- Serious adverse events (SAEs) will be recorded throughout the study period. Prior to vaccination, any SAEs due directly to study procedures will be captured. All SAEs will be captured, beginning with the administration of the first dose and ending 14 months after Dose 1 of study vaccine. After the double-blind phase of the study, all enrolled children will be visited at home monthly by field workers until study conclusion to ensure complete identification of all SAEs.
- Safety review process: safety data from the first 40 children to receive Dose 1 and Dose 2 will be reviewed by the DSMB to authorize progression to the next sequential dose.
- This study will not capture cases of malaria for the analysis of efficacy. All cases of malaria presenting during the unsolicited period will be captured as unsolicited events. Cases at anytime during the study that meet the criteria for a SAE will be reported as SAEs.
- The access of the study population to HIV voluntary counseling and testing and HIV antiretroviral therapy according to national recommendations will be ensured, in collaboration with the government services.
- An insecticide impregnated bednet will be offered to all parent(s)/guardian(s) who present their child for screening.

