**Clinic Visit 2: Vaccination 1**  
Day 0

---

- Check study identification card of vaccinee
- Take medical history and carry out physical examination, measure body weight
- Check contraindications to vaccination
- Check elimination criteria
- Record pre-vaccination body temperature

- Randomize subjects
- Administer the first dose of RTS,S/AS01E or RTS,S/AS02D intramuscularly in the left deltoid

Each child will be assessed for at least 60 minutes after vaccination to evaluate and treat any acute adverse events.

- Record any post-vaccination solicited symptoms
- Record any post-vaccination unsolicited adverse events
- Record any post-vaccination SAEs
- Record concomitant medication

---

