**Clinic Visit 5: Vaccination 3**

Day 60

- Check study identification card of vaccinee
- Check contraindications to vaccination
- Check elimination criteria
- Record unsolicited adverse events experienced by the vaccinee since the last visit
- Record pre-vaccination body temperature
- Administer the third dose of RTS,S/AS01E or RTS,S/AS02D intramuscularly in the left deltoid

Each child will be assessed for at least 60 minutes after vaccination to evaluate and treat any acute adverse events.

- Record any post-vaccination solicited symptoms
- Record any post-vaccination unsolicited adverse events
- Record any post-vaccination SAEs
- Record concomitant medication
- Blood sample to collect 5 mL blood for analysis of:
  - serology (antibodies to CS, HBs)
  - cell-mediated immunity and B-cell memory

---

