# **9. SUBJECT COMPLETION AND WITHDRAWAL**

## **9.1. Subject completion**

A subject who returns for the concluding visit/is available for the concluding contact foreseen in the protocol is considered to have completed the study.

A subject that comes for Clinic Visit 6 has completed the double-blind phase of the study. A subject that comes for Clinic Visit 7 has completed the single-blind phase of the study.

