### **10.3. Tertiary endpoints**

#### **10.3.1. Immunogenicity**

*At Study Month 14:*

- Anti-HBs antibody titers determined 12 months post Dose 3.
- Anti-CS antibody titers determined at 12 months post Dose 3.

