#### **10.3.2. Safety**

- Occurrence of SAEs from 1 month post Dose 3 until 12 months post Dose 3.

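### Visit 7 is timed from Dose 1 but its endpoints are set at 12 months after Dose 3, so SAE follow-up can close 12 to 40 days early for a child seen at Month 13

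*Protocol*

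**What the plan says.** Table 4 gives the Visit 2→Visit 7 interval as "14 months ± 1 month". Visit 2 is Dose 1 ("Clinic Visit 2: Vaccination 1", Section 5.11). Dose 3 is given at Visit 5 ("Clinic Visit 5: Vaccination 3", nominally Day 60), and Table 4 has no Visit 5→Visit 7 row. The text under Table 3 makes the intervals binding: "These intervals determine each subject's evaluability in the according to protocol analyses".

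The endpoints use the other anchor. Section 10.3.2 defines the tertiary safety endpoint as "Occurrence of SAEs from 1 month post Dose 3 until 12 months post Dose 3". Section 10.3.1 has "Anti-CS antibody titers determined at 12 months post Dose 3" and a matching anti-HBs endpoint, both under the label Study Month 14. The cellular endpoints in Section 10.4 also include a 12-month sample counted from Dose 3.

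The end of SAE capture is given in two ways. The synopsis has it "ending 14 months after Dose 1 of study vaccine", while Section 8.4 has it at study conclusion. For the individual child, Section 9.1 says "A subject that comes for Clinic Visit 7 has completed the single-blind phase of the study". Under Section 8.9, investigators need not actively look for events in former participants.

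The synopsis continues monthly home visits until study conclusion, whereas the visit list in Section 5.11 ends at Month 13.

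**The concern.** The two anchors agree only when Dose 3 falls close to Day 60 and Visit 7 close to Month 14. Elsewhere in the permitted ranges, a child can attend Visit 7 in full compliance and count as a completer before 12 months after Dose 3. A child seen at Month 13 also stops a month before the synopsis says SAE capture ends.

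Two things are at stake. The tertiary SAE period is not fully observed in children seen early. The titers and cellular results labelled as 12 months after Dose 3 also come from a range of sampling times wider than the ± 1 month suggests.

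**Working it through.** **Inputs, all from the protocol**
- Visit 7: 13 to 15 months after Dose 1 (Table 4).
- Dose 1 to Dose 2 and Dose 2 to Dose 3: 21 to 35 days each (Table 4).
- Nominal Dose 3: Day 60 (Section 5.11).
- Tertiary SAE period: month 1 to month 12 after Dose 3, that is 11 months (Section 10.3.2).

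The protocol does not define a month in days. Results are for 30-day months, with 30.44-day months in brackets where they differ.

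**1. The plan's own equivalence.** 14 × 30 − 60 = 360 days = 12.0 months after Dose 3. The nominal schedule is consistent.

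**2. Range of Dose 3.** 21 + 21 = Day 42; 35 + 35 = Day 70.

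**3. Visit 7 counted from Dose 3** (Visit 7 day minus Dose 3 day)
- Earliest: 390 − 70 = 320 days (326), or 10.7 months.
- Latest: 450 − 42 = 408 days (415), or 13.6 months.
- Spread: 88 days (89), or 2.9 months. This is the extreme; with Dose 3 on Day 60 the range is 11 to 13 months.

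**4. Shortfall for a child seen at Month 13.** This is 12 months − (13 months − Dose 3 day) = Dose 3 day − 1 month.

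| Dose 3 | Shortfall | Share of 11 months (330 days) |
|---|---|---|
| Day 42 | 12 days | 3.6% |
| Day 60 | 30 days | 9.1% |
| Day 70 | 40 days | 12.1% |

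The shortfall is positive for every permitted Dose 3 date. With Dose 3 on Day 70, a visit at exactly Month 14 is still 70 − 60 = 10 days short (9).

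**5. Average loss, under an assumption.** With Dose 3 on Day 60 and visits spread evenly over Months 13 to 15, half the children are seen early, by half a month on average: 0.5 × 0.5 = 0.25 month, or about 2% of 11 months.

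**6. Effect on titers, under assumptions.** Borrow the log SD of 0.9 from Section 10.5, read as log10, and spread visits evenly over the full 2.92 months, so the SD of timing is 2.92/√12 = 0.84 month. The protocol gives no decay rate, so take two half-lives:
- 3 months: slope 0.301/3 = 0.100 log10 per month; √(0.9² + (0.100 × 0.84)²) = 0.904, an increase of 0.4%.
- 1 month: slope 0.301; √(0.9² + (0.301 × 0.84)²) = 0.935, an increase of about 4%.

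**7. After re-anchoring.** With 12 months ± 1 month from Visit 5, Visit 7 falls 11 to 13 months after Dose 3, a spread of 60 days (61). The latest visit is 13 months + 70 days = 15.3 months after Dose 1. An early visit could still precede 12 months, so re-anchoring alone does not complete the SAE period.

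**The case against.** A tolerance of one month either side of a year is ordinary for descriptive follow-up. The window is the same in both randomized groups, the Month 14 results are tertiary or exploratory with no non-inferiority test, and the largest shortfall needs the latest Dose 3 together with the earliest Visit 7. All of this stands and keeps the point minor. It does not remove the mismatch, because a Month 13 visit is short under every permitted Dose 3 date.

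It can also be said that no section names the Visit 7 date as the end of SAE collection, and that study conclusion in Section 8.4 may mean the end of the whole trial. That is fair as a reading. In practice, though, no contact with the child is scheduled after Visit 7, and Section 8.9 removes any duty to look.

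Two stronger readings are tempting, and the documents do not support them.
- A reader might infer that a Month 15 visit leaves two months without active SAE capture, since the visit list in Section 5.11 stops at Month 13. The synopsis, however, continues monthly home visits until study conclusion, Visit 7 itself asks about SAEs since the previous visit, and hospital surveillance (Section 5.7.1) runs throughout. What remains is a list that does not match the synopsis.
- A reader might infer that the SAE proportion is biased low. Late visits can add events beyond the stated period, and the annex table (Section 10.9.1) runs from study start to study conclusion rather than over the 11-month slice. The supportable statement is that follow-up is incomplete for children seen early.

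**Conclusion.** The point holds as a minor inconsistency. Visit 7 is anchored to Dose 1 while everything read at it is defined from Dose 3. A compliant Month 13 visit closes a child about 12 to 40 days before the tertiary SAE period ends, and a month before the SAE end in the synopsis. The individual maximum is about 12% of the period; the average is about 2% under even spacing with Dose 3 on Day 60.

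The sampling-time spread adds little to the GMTs: 0.4% to 4% on the SD for the half-lives assumed. No between-group bias is expected, and the Day 90 coprimary endpoints are unaffected. The date results rest only on the Table 4 intervals and the length taken for a month; the average loss and the SD figures rest on the stated assumptions.

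**What to change.** - In Table 4, replace the Visit 2→Visit 7 row with Visit 5→Visit 7 at 12 months ± 1 month. Keep the Visit 2 anchor for children who did not receive Dose 3, since under Section 5.4 they continue the other study procedures.
- For any child seen before 12 months after Dose 3, add one routine field-worker SAE contact at that date.
- Count tertiary SAEs to 12 months after Dose 3 for every child who received it.
- Align the synopsis (end of SAE capture), Section 8.4 (study conclusion) and the field-visit list in Section 5.11 (end at Month 13) with this rule.

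The window stays two months wide, so the interval that decides ATP evaluability is not tightened. A one-sided window opening only at 12 months would avoid the extra contact, but it would halve that interval and could cost evaluable children.

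The cost is one table row, a few aligned sentences, one extra field-worker contact for some children, and slightly later visits for some, up to about 15.3 months after Dose 1 instead of 15.
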